## Abstract

**Background:**

The extent of resection of glioma is one of the most important predictors of the survival duration of patients after surgery. The presence of eloquent areas within or near a tumor often limits resection, as resection of these areas would result in functional loss and reduced quality of life. The aim of this randomized, triple-blind, sham-controlled study is to investigate the capability of repetitive navigated transcranial magnetic stimulation (rnTMS) over the primary motor cortex to facilitate the functional reorganization of the motor network.

**Methods:**

One hundred forty-eight patients with tumors in movement-relevant areas will be included in this randomized, sham-controlled, bicentric, triple-blind clinical trial. Patients considered at high risk for postoperative motor deficits according to an initial nTMS assessment will receive inhibitory rnTMS at 1 Hz for 30 min followed by a short motor training of 10 min. Stimulation will be applied to the fiber endings of the corticospinal tract closest to the tumor based on individualized tractography. Stimulation will be performed twice daily for each 30 min for 5–28 days depending on the individually available time between study inclusion and surgery. The intervention is controlled by a sham stimulation group (1:1 randomization), where a plastic adapter will be placed on the coil. We expect a comparable or better motor status 3 months postoperatively as measured by the British Medical Research Council (BMRC) score for the affected upper extremity (non-inferiority) and a higher rate of gross total resections (superiority) in the rnTMS compared to the sham group.

**Discussion:**

The generated reorganization of the brain’s areas for motor function should allow a more extensive and safer removal of the tumor while preserving neurological and motor function. This would improve both survival and quality of life of our patients.

**Trial registration:**

DRKS.de DRKS00017232. Registered on 28 January 2020.

**Supplementary Information:**

The online version contains supplementary material available at 10.1186/s13063-023-07640-2.

## Administrative information

Note: the numbers in curly brackets in this protocol refer to SPIRIT checklist item numbers. The order of the items has been modified to group similar items (see http://www.equator-network.org/reporting-guidelines/spirit-2013-statement-defining-standard-protocol-items-for-clinical-trials/).

## Introduction

### Background and rationale {6a}

Around 8300 cancers of the central nervous system and 6140 deaths are reported in Germany every year [1]. These cancers are associated with 150,993 disability-adjusted life years reported in 2016 [1]. Furthermore, an increase in sick leave is observed in these patients before surgery with a return-to-work rate of only 50% 1 year after surgery [2], thus presenting a major socioeconomic burden. While maximal surgical resection has been linked with improved overall survival, up to 50% of intrinsic brain tumors are not completely resected due to infiltration of functional brain tissue. In addition, up to 25% of patients with brain tumors in motor areas suffer from new or worsened motor deficits postoperatively. Both, incomplete tumor resection and impaired neurological status, are directly correlated with decreased life expectancy [3, 4]. While surgical resection is the most effective treatment option for intrinsic brain tumors, traditionally, tumors that have been demonstrated to infiltrate functional tissue will be diagnosed as inoperable and will be treated conservatively from then on. However, in recent years the concept of neurological functions being confined to specific areas of the brain has been questioned and a novel concept of function being represented in dynamic cortico-subcortical networks has been introduced [5]. This paradigm shift also implies that function can move, for example, due to the presence of a pathology — yet typically, the reshaping is too slow or ineffective to sustainably affect the clinical course of the patient.

A way to increase the extent of resection and improve prognosis would be to promote functional reorganization, where brain areas distant from the tumor take over behavioral functions of eloquent areas at risk. Several case studies have shown proof-of-concept that (non)invasive cortical stimulation can facilitate plastic reorganization in brain tumor patients leading to higher resection rates and improved functional outcomes [6–8]. The most recent of these studies [7] applied direct cortical stimulation to tumor-invaded eloquent brain areas via implanted grid electrodes for approximately 16 days after a partial tumor resection in five patients. They were able to induce functional reorganization in all cases, thus enabling a second surgery with the removal of the former eloquent brain areas without permanent functional deficits. However, many patients suffered from severe side effects such as cerebral seizures. A case study examining a patient with a tumor in Broca’s area applied theta burst stimulation over 12 consecutive days using rTMS to induce plasticity in language areas and observed no severe side effects [8]. However, changes in functional connectivity were only visible in magnetoencephalography measurements but did not influence the extent of resection.

Recent studies investigate more intense stimulation protocols, applying rTMS multiple times per day [9]. These studies showed that days of treatment can be reduced significantly, while reaching similar or higher efficacy. Furthermore, a recent pilot study found no increase in side effects in an accelerated low-frequency repetitive neuronavigated TMS (rnTMS) protocol compared to conventional once-daily rnTMS [10]. A recent clinical trial [11] provided the first evidence for rnTMS to facilitate recovery of postoperative motor deficits in brain tumor patients. Here, already, a stimulation duration of 7 days led to a significantly better motor function compared to the sham group with a number needed to treat of only 2.19. A following clinical trial [12] replicated these results with slightly lower effect sizes. No previous study has investigated the here proposed preconditioning approach of preoperative rnTMS on postoperative clinical and neurooncological outcomes so far.

### Objectives {7}

#### Primary hypotheses

We hypothesize that preoperative rnTMS can induce a functional reorganization of the stimulated motor network, leading to (a) a comparable or better motor status (British Medical Research Council (BMRC) score for upper extremities) 3 months postoperatively (T3) (non-inferiority), and (b) a higher gross total resection rate (superiority) in the rnTMS group compared to the sham group.

#### Secondary hypotheses

The induced functional reorganization will be visible in stronger changes of functional connectivity from baseline to the time point after the intervention (T1) in the intervention group compared to the sham group. Furthermore, rTMS treatment will lead to better health-related quality of life (European Organization for Research and Treatment of Cancer Quality of Life Questionnaire Brain Tumor Module (EORTC QLQ BN20)) and motor function (Action Research Arm Test (ARAT)) compared to the control group at 7 days (T2) and 3 months postoperatively (T3).

### Trial design {8}

The trial is designed as a randomized, triple-blind, sham-controlled, bicentric parallel-group two-arm non-inferiority trial. Patients will be allocated 1:1 to the two groups. Patients, outcome assessors, and the trial statistician will be blinded to the group allocation. An overview of the trial timeline can be found in Fig. 1.

**Fig. 1 Fig1:**
[figure not shown]
The diagram summarizes the trial intervention scheme and trial flow. Patients are screened for inclusion and exclusion criteria (see {10}). Participation in the study is offered to all eligible patients and patients agreeing to participate will be randomized (see {16}). Equal numbers of patients will be allocated to an intervention and sham-controlled group (see {6b, 11a}). After the intervention, patients will complete one follow-up before surgery as well as two follow-ups postoperatively (see {12, 13}). All randomized patients will be included in the analysis in an ITT framework (see {20})

## Methods: participants, interventions, and outcomes

### Study setting {9}

All study procedures and rnTMS sessions will be performed at the Charité Berlin and Heidelberg University Hospital. Patients will be recruited from the regular incoming patients. Figure 1 gives an overview of the trial design and patient flow. A current list of participating study sites can be obtained from the coordinating investigator and on the trial register (DRKS00017232), if additional study sites will be included during the course of the study (for example to increase recruitment numbers).

### Eligibility criteria {10}

Subject inclusion criteriaSuspected supratentorial glioma grade II-IV in a motor-relevant area based on preoperative (Magnetic Resonance Imaging (MRI)Infiltration of primary motor cortex or distance between tumor and corticospinal tract below 8 mm [13] based on results of preoperative nTMS assessment and following tractography of the corticospinal tractStudy participation does not delay surgeryAge ≥ 18 years at the time of signing the informed consentAbility to give written informed consent subject exclusion criteriaContraindications for receiving an MRI as assessed by the attending neuroradiologistContraindications for undergoing a TMS examination as assessed by the attending neurosurgeonSurgery scheduled within < 5 days after screening for inclusion criteriaMore than one seizure per week based on patient reports or medical recordsPregnancyMissing informed consent

### Who will take informed consent? {26a}

Incoming patients will be screened for eligibility by a study physician during ambulatory care visits or admission to the neurosurgical ward. Eligible patients will be informed about the study procedures and provided with a written study information and informed consent form. Potential study patients will be given at least 24 h between study information and the provision of consent. Consent forms contain a declaration of data privacy and protection alongside contact information in case of questions or complaints. Consent will be obtained in written form and has to be signed by the patient and study physician.

### Additional consent provisions for collection and use of participant data and biological specimens {26b}

The study consent form includes a series of opt-in questions on data reuse and sharing that will not affect participation in the trial itself. Patients can choose to agree to these questions or reject them individually. No biological specimens will be collected.

## Interventions

### Explanation for the choice of comparators {6b}

Participants in the control group will receive sham stimulation over the affected motor cortex followed by a short motor training. The sham rnTMS protocol in this study uses a custom-made plastic adapter placed on the stimulation coil, avoiding the induction of a meaningful electric field at the cortical level. This sham setting elicits a sound comparable to real rnTMS as it allows stimulation at the same intensity as during the real rnTMS intervention.

### Intervention description {11a}

Participants in the intervention arm will receive rnTMS over the affected motor cortex using a Nexstim NBS 5 stimulator with neuronavigation (Nexstim, Helsinki, Finland) followed by a short motor training. The stimulation target is selected by combining TMS with tractography. Functional fibers of the corticospinal tract closest to the tumor and hence, most endangered by resection of the tumor, are identified. RnTMS will be centered over the cortical endings of those fibers. Stimulation is applied at 1 Hz [14] and an intensity of 110% [10]. The duration of the intervention is 30 min per session twice daily (90 min apart) over multiple days to maximize the treatment dose in the short preoperative time [9]. The individual study duration depends on the time available before surgery (≥ 5 days, maximum 28 days). While we assume that longer trial durations will maximize the effects and clinical impact of the stimulation [8, 15], the effects of rnTMS have already been shown after a single session [16]. A short motor training of 10 min will be applied after rnTMS stimulation to facilitate the recruitment of additional networks for motor function while motor fibers in danger during surgery are temporarily inhibited [7]. A set of exercises has been established together with physiotherapists, allowing adaption of the training based on participants’ abilities. See also {13} for a detailed description of the participant timeline and procedures performed at each timepoint.

### Criteria for discontinuing or modifying allocated interventions {11b}

Patients can withdraw from the trial on their own wish at any point without any disadvantages. They will also be released from the trial in case of immediate need for surgery, for example, due to a progressing tumor, or conflicting recommended or necessary medical treatments. Occurrence of serious moderate, serious or severe, life-threatening, or fatal adverse events will lead to exclusion of the participant. In case of moderate, but not serious adverse events treatment may be continued, modified, or discontinued based on the judgment of the independent Data and Safety Monitoring Board (DSMB).

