## Statistical methods

### Statistical methods for primary and secondary outcomes {20a}

#### Efficacy

To test both main hypotheses of comparable motor status at T3 and a higher GTR in rnTMS patients compared to sham patients, we will apply hierarchical testing at a two-sided significance level of *α* = 0.05 (Power = 80%). Primary hypotheses will be tested in an intention-to-treat (ITT) framework using multiple imputed datasets in case of missing values (under the assumption of MCAR or MAR) after a single imputation of informative missing values (MNAR) for example for patients with worsened health status or patients who die during follow up.

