### Methods in analysis to handle protocol non-adherence and any statistical methods to handle missing data {20c}

Primary hypotheses will be tested in an ITT framework. The primary population is defined as all randomized patients with a baseline measurement of the primary endpoints. Both primary hypotheses will be tested hierarchically at a two-sided significance level of 0.05. To account for possible dropouts (approximately 10%), 148 patients in total will be included in the study to ensure at least 132 complete cases, even if we apply missing value imputation methods using 30 complete data sets (if MAR or MCAR assumption holds). To evaluate if individual missings are MAR, MCAR, or MNAR we will use information on reasons of missings or dropout (e.g. if patients drop out due to worsening of health status or not). In case of premature death (before measuring the primary outcome), the BMRC score for those patients will be set to the worst possible value.

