### Adverse event reporting and harms {22}

All (serious) adverse events ((S)AEs) will be collected from the date the informed consent form is signed until the final study visit. For events that occur between postoperative follow-ups, participants are queried on a routine basis about every 2 weeks starting from postoperative day 7. (S)AEs will be captured on case report forms according to MedDRA, including event description; time of onset; assessment of seriousness, severity, relationship to study procedures or interventions, and expectedness; medical care received; outcome of event; and time of resolution/stabilization of the event. All (S)AEs occurring during the trial are documented appropriately regardless of their relationship to the intervention. All (S)AEs will be followed until satisfactory resolution or the participant is stable. All (S)AEs will be assessed by the investigator for severity, expectedness, and relationship to the intervention using the protocol-specified definitions.

Documentation of AEs will be reported to Clinical Trial Management within 7 days. All AEs are reported in aggregate as part of the routine data and safety monitoring report provided to the DSMB and the BMBF/DLR by the Clinical Trial Management. AEs are reported to the IRB as part of the continuing review. SAEs (regardless of expectedness or relatedness) will be reported to the DSMB and BMBF/DLR within 48 h of the investigator becoming aware of the event. Previous trials of the same duration and similar doses did not show any SAEs related to the intervention.

Based on our previous trial on postoperative rnTMS therapy (SAE = 0, AE = 0 in 16 patients with each 7 rnTMS sessions; see in [12]) and pilot study on accelerated rnTMS in healthy subjects (SAE = 0, AE = 5 in 3 subjects with each 14 rnTMS sessions; see in [10]), we expect AEs: *n* = 30 (mild headache); *n* = 50 (tiredness due to intensive stimulation and training); *n* = 10 (dizziness); SAEs: *n* = 0.

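### Participants with serious events or urgent surgery are to leave the trial, which conflicts with the intention-to-treat rules and gives up observable motor outcomes

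*Protocol article*

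**What the plan says.** Section {11b} of the protocol article sets two rules for leaving. For adverse events: "Occurrence of serious moderate, serious or severe, life-threatening, or fatal adverse events will lead to exclusion of the participant". For urgent surgery: "They will also be released from the trial in case of immediate need for surgery, for example, due to a progressing tumor". The sentence that follows the adverse-event rule, on moderate non-serious events, speaks only of treatment being continued, modified or discontinued. The section thus uses different terms for stopping treatment and for leaving the trial.

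The collection window in {22} is long: "All (serious) adverse events ((S)AEs) will be collected from the date the informed consent form is signed until the final study visit". Events are documented whatever their relationship to the intervention.

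The analysis rules point the other way. The legend of Fig. 1 says: "All randomized patients will be included in the analysis in an ITT framework". Section {20c} narrows this: "The primary population is defined as all randomized patients with a baseline measurement of the primary endpoints". The Efficacy paragraph of {20a} plans multiple imputation "after a single imputation of informative missing values (MNAR) for example for patients with worsened health status or patients who die during follow up". For deaths, {20c} states: "In case of premature death (before measuring the primary outcome), the BMRC score for those patients will be set to the worst possible value". The GTR part of the sample size section {14} repeats the rule for deaths.

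**The concern.** Taken literally, {11b} ends a patient's participation, not only the remaining stimulation sessions. A serious postoperative event weeks after the last session would trigger it when no stimulation is left to stop, and the 3-month (T3) motor assessment would not be made. Nothing shown says that T2 and T3 visits continue after exclusion or release.

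These patients are likely to have poor motor status, and motor status at T3 is the gatekeeper: it is tested for non-inferiority against an odds ratio of 1.35, and GTR is tested only if that succeeds ({20a}). In a non-inferiority comparison, selective loss of poor outcomes from the active arm can make the arms look more alike than they are. Even without such selection, the result rests more on imputation than it needs to.

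**Working it through.** **1. The plan's own figures.** Dropout: 132 / (1 − 0.10) = 146.7, so 147, or 148 for an even 1:1 total; the plan states 148. GTR power with 66 per arm, 74% vs 50%, two-sided 0.05:

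- pooled proportion 0.62; √(2 × 0.62 × 0.38) = 0.686; √(0.74 × 0.26 + 0.50 × 0.50) = 0.665
- z = (0.24 × √66 − 1.96 × 0.686) / 0.665 = 0.909, so power 81.8%; the plan states 82%

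Both reproduce. The point disputes no stated figure; it is about rules that do not fit together.

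**2. The rules side by side.**

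| Situation | {11b} | Fig. 1, {20a}, {20c} |
|---|---|---|
| Fatal event | excluded | worst BMRC score, so retained |
| Non-fatal serious event | excluded, no limit on relatedness or time | analysed as randomised; T3 value imputed if missing, imputed value not stated |
| Immediate surgery | released from the trial | analysed as randomised; further data collection not stated |
| Missing baseline | not addressed | Fig. 1: analysed; {20c}: not in the primary population |

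For comparison, the trial-level rules in {21b} apply only where a relationship to the intervention is assumed or cannot be ruled out. {11b} has no such condition.

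The baseline condition in {20c} refers to both primary endpoints. GTR is defined in {12} as no detectable residual tumour on the postoperative MRI, so it has no baseline value.

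**3. How many patients.** The allowance is 148 − 132 = 16. The Background gives up to 25% new or worsened motor deficits after surgery in such patients, that is up to 0.25 × 148 = 37. If 16 / 37 = 43% of these were classed as serious (an assumption), this route alone would use up the allowance.

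If exclusions came on top of the planned 10% and GTR were lost too, 5% more would leave 148 × 0.85 = 125.8 patients (GTR power about 80%), and 10% more would leave 148 × 0.80 = 118.4 (about 77%). The effect on power is small.

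**4. What deletion would do to the odds ratio.** Assumptions: true OR at the margin, 1.35; 50% worse outcome in sham; hence 1.35 / 2.35 = 57.4% in rnTMS. A fraction e of an arm is deleted, and a share q of those deleted had a worse outcome. The remaining proportion is (p − e·q) / (1 − e).

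Example, 10% vs 5% with q = 1: rnTMS (0.574 − 0.10) / 0.90 = 0.527, odds 1.115; sham (0.50 − 0.05) / 0.95 = 0.474, odds 0.900; OR = 1.115 / 0.900 = 1.24.

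| Deleted, rnTMS vs sham | OR, q = 0.8 | OR, q = 1.0 |
|---|---|---|
| 5% vs 5% | 1.37 | 1.37 |
| 5% vs 2% | 1.32 | 1.28 |
| 5% vs 0% | 1.29 | 1.23 |
| 10% vs 5% | 1.30 | 1.24 |
| 10% vs 0% | 1.22 | 1.12 |

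Of 74 per arm, 5% is 3.7 patients and 10% is 7.4. The shift towards non-inferiority appears only when rnTMS loses more patients. These figures describe deletion, not imputation. They would apply to the complete-case sensitivity analysis, and to the primary analysis only if exclusion were taken to mean leaving the analysis set.

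**The case against.** The strongest reply is that {11b} does not govern the analysis at all. Its heading concerns the allocated intervention, and the analysis population is set in Fig. 1, {20a} and {20c}. Deaths get the worst score, informative missing values are singly imputed, and reasons for dropout are used to classify the rest. Section {18b} expects about 2% missing BMRC and no missing GTR, and {22} follows adverse events until resolution or stability. All of that fits a reading in which only treatment stops.

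This stands in so far as a reader might infer from {11b} that these patients are removed from the analysis. No section says so.

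A reader might also infer that the rule biases the trial towards non-inferiority. That does not follow. Without a relatedness condition, surgical and tumour events count in both arms; outcome assessors and surgeon are blinded; and {21b} provides for stopping the trial or revising the design if serious events are thought related.

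Nor is it enough to show an odds ratio falling below 1.35. Take a worse outcome in 33.3% vs 25% (OR 1.50), and delete patients with worse outcomes amounting to 10% of the rnTMS arm and 5% of the sham arm. The OR becomes (0.2333 / 0.6667) / (0.20 / 0.75) = 1.31. With 74 per arm the remaining cells are about 17.3 / 49.3 and 14.8 / 55.5, the standard error of the log OR is 0.40, and the upper 95% limit is about 2.9. The criterion in {20a} is that upper limit, so non-inferiority would not be declared.

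The reply does not remove the conflict in wording. The next sentence of {11b} shows that its authors had a term for stopping treatment and did not use it in these two rules. On the treatment-only reading, listing fatal events has no purpose; on the literal reading, it contradicts {20c}. The safeguards state an imputed value only for death. The expectation in {22} of no SAEs is drawn from 16 patients and 3 healthy subjects in stimulation studies, so it says little about surgical events.

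**Conclusion.** The concern holds as a conflict between sections with a practical consequence. If {11b} is followed as written, T3 motor scores that could have been observed are not collected in patients likely to do badly, and a gatekeeping non-inferiority test depends on imputation in their place. If exclusion is read as leaving the analysis, intention-to-treat is broken; the document neither says this nor rules it out.

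The size cannot be fixed, because no exclusion rates, overall or by arm, are given. Under the assumptions shown, deletion would move an OR of 1.35 to between 1.12 and 1.32 if rnTMS lost more patients, and would leave it at about 1.37 if losses were equal. An established bias towards non-inferiority is therefore not supported.

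The baseline condition in {20c} is a smaller matter. Baseline BMRC is taken before stimulation, so its absence should not depend on arm, but the definition does not fit GTR.

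**What to change.** Reconcile {11b}, Fig. 1, {20a} and {20c}. The clinical decision on stopping stimulation is not at issue. The text should say:

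- Whatever that decision is, these events end the study intervention only. T2, T3 and GTR are still collected and analysed in the randomised arm unless the patient withdraws consent.
- Deaths are described in {11b} in a way that agrees with the worst-score rule in {14} and {20c}.
- How a missing T3 BMRC is imputed after a non-fatal serious event or urgent surgery.
- The primary population is all randomised patients for both endpoints. A missing baseline BMRC, needed for adjustment, can enter the multiple imputation already planned.

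The cost is an amendment of wording and follow-up of a few more patients. According to {18b}, T2 takes place before discharge, T3 coincides with regular follow-up visits, and the postoperative MRI is routine, so little is added.
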